**Table 1 Tab1:**
[figure not shown]
Participant timeline: schedule of enrolment, interventions, and assessments

**Fig. 1 Fig1:**
[figure not shown]
CONSORT diagram

### Recruitment {15}

Strong partnerships with schools were built through ongoing engagement activities between Universidad del Norte and local schools, beginning in 2022, which helped foster sustained interest and collaboration. Local organizations, such as Univoluntario, are involved in the project and have good connections with schools. All schools are approached via email, followed up with personal visits to the schools to present the project and receive approval from the school director. Parental consent forms will be collected during and after parent information events before the start of data collection.

Intervention sessions will be conducted during school hours, to maximize participant engagement and availability. Participants will receive little gifts (e.g. keyrings, wristbands) and snacks; the schools will receive books to thank them for their time and effort.

## Assignment of interventions: allocation

### Sequence generation {16a}

Random blocks will be used to assign participating schools according to their SES (high vs. low) and geographical area (rural vs. urban), resulting in three different blocks: rural/low SES; urban/high SES; urban/low SES. In each block, schools will be randomly assigned to either the intervention or treatment group. The allocation sequence will be determined using computer-generated random numbers from Researchrandomizer.org.

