**Methods:**

We will recruit 1250 adolescents in 7th–10th grade (aged 11–17 years) to participate in a two-arm, cluster-randomized, open-label, controlled superiority trial in Colombia. Participating schools will be recruited by the research team. Participants will be randomized at the school level (1:1). Randomization blocks stratified by socioeconomic status (high vs. low) and geographical area (rural vs. urban) will be used to assign schools to either: (a) a school-based, four-session group intervention delivered over 2–4 weeks by trained facilitators (*n* = 625) or (b) a waitlist control group that will receive the intervention only after follow-up (*n* = 625). Participants need to be aged 11–17 years old, attending a participating school and class in grades 7 to 10, have written parental consent, and give written assent to be eligible for participation in this study. Individuals who cannot understand spoken or written language, or who do not have parental consent to participate, will be excluded. Primary outcomes are media literacy and body dissatisfaction. Secondary outcomes include appearance comparison, thin ideal internalization, curvy ideal internalization (girls only), drive for muscularity (boys only), eating disorder symptoms, and general wellbeing. Additional exploratory outcomes include risky appearance-altering behaviours (girls only), colourism, and skin colour satisfaction. Furthermore, adverse outcomes will be recorded.

Outcome assessments will happen pre-intervention (baseline; Timepoint 1), 1-week post-intervention (immediate post-test; Timepoint 2), and 9–12 months post-intervention (follow-up; Timepoint 3).

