### Trial design {8}

In this two-arm cluster-randomized, open-label, controlled superiority trial, we will compare changes in primary and secondary outcomes in participating adolescents randomized to receive either the intervention or a wait-list control condition in a parallel group design over the first 9–12 months of the study. The group allocation ratio is 1:1, clustered by school and stratified by geographical location (urban/rural), socioeconomic position (high/low), and funding status (state/private). Participants in the waitlist control group will receive the intervention after follow-up data collection is concluded.

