### Participant timeline {13}

#### Sample size {14}

The trial aims to detect small between-group effects of our outcomes. The pilot trial in Colombia (*N* = 338) showed that the smallest effect size was approximately *d* = 0.3 (body dissatisfaction in boys); we aimed for a slightly lower effect size of *d* = 0.25. For the primary sample-size calculation, we assumed a two-sided significance level of *α* = 0.05, 80% power (1 − β = 0.80), and equal allocation to two arms (intervention vs. control), yielding 251 participants per arm. Because this trial uses a cluster-randomized design, sample size calculations incorporated clustering effects, including ICC (intraclass correlation coefficient) and DE (design effect), which determines how much the sample size needs to be inflated compared to an individually randomized trial). Based on the pilot trial in Colombia, we assumed an average group size of *m* = 25 and an ICC of 0.046, which requires 529 participants per arm. We allowed for 10% attrition, yielding a sample size of 611 participants and 1250 participants in total (see Table 1 and Fig. 1).

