## Statistical methods

### Statistical methods for primary and secondary outcomes {20a}

Data will be analysed using RStudio [30]. First, data will be assessed for completely missing at random using Little’s test (MCAR) [31]. If data is missing at random (MAR), we will employ linear mixed-effects models to examine the effects of the intervention, using the Maximum Likelihood approach. If data is not missing at random, we will employ Multiple Imputation. The number of imputations will be decided based on m≈ %missing (as recommended by [32]). Furthermore, we will run MNAR sensitivity analyses (pattern-mixture/delta) [33].

Each outcome will be analysed using a linear mixed-effects model including the baseline measure of the outcome, gender, and the interaction between gender (boys vs. girls) and group (intervention vs. control) as fixed effects, along with timepoint (baseline, immediate post-test, follow-up). Random intercepts will be included for participant (to account for repeated measures) and nested clustering of classes within schools to reflect the cluster-randomized design. Analyses will be conducted separately for each outcome variable; primary outcomes will be used for confirmatory inference, while secondary and exploratory outcomes will be analysed separately with appropriate multiple-comparison adjustment as required. To estimate effect sizes, we will calculate partial eta squared. Following Cohen’s [34] guidelines, values of 0.01, 0.06, and 0.14 will be interpreted as small, medium, and large effects, respectively [34].

Subgroup analyses will be conducted based on baseline scores for each outcome variable, comparing participants with high versus low initial levels (categorized using median splits of baseline scores). In addition, moderator analyses will include interactions between each moderator and group to examine the potential influence of gender, socioeconomic status (high vs. low), location (urban vs. rural), and school type (state vs. private) on intervention effects.

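### The protocol names three stratification factors in one place and two in others, and the listed outcome model contains no randomisation factor, which makes the test somewhat conservative

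*Protocol article*

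**What the plan says.** The allocation is described in three places of the protocol article.

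- Abstract, Methods: "Randomization blocks stratified by socioeconomic status (high vs. low) and geographical area (rural vs. urban) will be used to assign schools". Two factors.
- Trial design {8}: "clustered by school and stratified by geographical location (urban/rural), socioeconomic position (high/low), and funding status (state/private"). Three factors.
- Sequence generation {16a}: "Random blocks will be used to assign participating schools according to their SES (high vs. low) and geographical area (rural vs. urban"). Two factors. The same section then gives a closed list of what these two factors produce: "resulting in three different blocks: rural/low SES; urban/high SES; urban/low SES".

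Statistical methods {20a} describes the model for each outcome as "including the baseline measure of the outcome, gender, and the interaction between gender (boys vs. girls) and group (intervention vs. control) as fixed effects", with timepoint alongside. Random intercepts are specified for participant and for "nested clustering of classes within schools to reflect the cluster-randomized design". The allocation factors come up afterwards, as effect modifiers: "In addition, moderator analyses will include interactions between each moderator and group", where the moderators are gender, SES, location and school type. Methods for additional analyses {20b} repeats this for SES, area and school type.

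**The concern.** There are two linked problems.

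First, a reader cannot tell which factors the randomisation controls. School type is a planned moderator. Anyone relying on Trial design {8} would take state and private schools to be split evenly between arms by design. Under Sequence generation {16a} that is left to chance.

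Second, the arms are compared between schools, so what the model does with between-school variance matters. Stratified allocation removes block differences from the true sampling variance of the treatment effect. A model without the blocks still counts those differences as unexplained school variance, and its standard error is too wide. The school random intercept does not cure this, because it is where the block differences end up. At stake are confidence intervals wider than they need be and some lost power on the confirmatory outcomes.

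**Working it through.** **Contradiction.** SES (2 levels) by area (2 levels) gives 4 cells. Leaving out rural/high SES gives the 3 blocks of {16a}. Adding funding status would give up to 8 cells, or up to 6 without rural/high SES. A list of exactly three blocks has no room for it, so {8} and {16a} cannot both hold.

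**The plan's own figures (Sample size {14}).** Inputs: d = 0.25 ("we aimed for a slightly lower effect size of *d* = 0.25"), two-sided alpha 0.05, power 0.80, m = 25, ICC = 0.046, 10% attrition.

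- Per arm without clustering: 2 × (1.960 + 0.842)² / 0.25² = 251.2 (stated 251).
- Design effect: 1 + 24 × 0.046 = 2.104. Then 251 × 2.104 = 528.1, so 529 (stated 529).
- 529/0.9 = 588, not the stated 611. Rounding to whole clusters does give it: 22 × 25 = 550 and 550/0.9 = 611, then 25 × 25 = 625 per arm and 1250 in total. The protocol does not describe this rounding. It does suggest 25 clusters of 25 per arm as a layout for illustration.

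No stratification factor enters this calculation.

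**Cost of leaving the blocks out (illustration).** Let J be the clusters per arm, m the number analysed per cluster, and R the share of between-cluster variance explained by blocks. R is an assumption.

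- V0 = (2/J)(ICC + (1 − ICC)/m): the variance that the model without blocks estimates.
- V1 = (2/J)(ICC(1 − R) + (1 − ICC)/m): the true variance under balanced stratified allocation, and the variance that the model with blocks estimates.

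Take J = 25 and m = 25 × 0.9 = 22.5, so (1 − ICC)/m = 0.954/22.5 = 0.0424 and V0 = 0.08 × 0.0884 = 0.00707. For R = 0.25, V1 = 0.08 × (0.0345 + 0.0424) = 0.00615. For R = 0.50, V1 = 0.08 × (0.0230 + 0.0424) = 0.00523.

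Without blocks, actual alpha = 2[1 − Φ(1.96√(V0/V1))] and power = Φ((0.25 − 1.96√V0)/√V1). With blocks, power = Φ(0.25/√V1 − 1.96).

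| R | V0/V1 | Actual alpha, no blocks | Power, no blocks | Power, with blocks | Difference |
|---|---|---|---|---|---|
| 0 | 1.000 | 0.050 | 0.844 | 0.844 | 0 |
| 0.25 | 1.150 | 0.036 | 0.861 | 0.890 | 2.9 points |
| 0.50 | 1.352 | 0.023 | 0.881 | 0.933 | 5.2 points |

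A simulation of cluster means with t-tests (strata of 16, 18 and 16 clusters, 10,000 trials per cell) gave power 0.842 against 0.871 at R = 0.25 and 0.858 against 0.918 at R = 0.50. Alpha without blocks was 0.038 and 0.021; with blocks it was 0.052 and 0.048.

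**Sensitivity to the number of schools.** Schools are randomised, and one school may supply several classes. With about 25 schools of 50, and the same ICC assumed to hold at school level, the formulas give 0.690 against 0.754 (R = 0.25) and 0.711 against 0.844 (R = 0.50).

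**Sensitivity to baseline adjustment.** Assume a baseline correlation of 0.8 at school level and 0.6 within schools, with blocks explaining 5–15% of what is left between schools. With 22.5 per cluster:

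- Between: 0.046 × (1 − 0.64) = 0.01656.
- Within: 0.954 × (1 − 0.36)/22.5 = 0.02714.
- Sum: 0.04370 without blocks, 0.04287 (5%) or 0.04122 (15%) with them.
- Standard error too large by √(0.04370/0.04287) − 1 = 1%, or √(0.04370/0.04122) − 1 = 3%.

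**The case against.** The strongest reply grants the contradiction and disputes the weight of the modelling point.

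- The list in {20a} is condensed. It does not separately name a group main effect or a group-by-time term, although Objectives {7} needs them, so a missing block term is weaker evidence than it would be in a full model statement. A separate analysis plan may add it. This stands in part. Still, the text does place SES, location and school type, and it places them only in additional interaction analyses, which answer a different question.
- Baseline adjustment should absorb much of any stable difference between blocks. This stands: only what blocks predict beyond baseline counts, and the loss may be very small.
- The error is conservative, and in the 50-cluster illustration power stays above the planned 80% either way. This also stands.

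A reader might go further and apply an assumed 20–50% reduction to the ICC of 0.046. The design effect would fall from 2.104 to 1.883–1.552, and one could claim 10–26% of the sample. The protocol does not support that. According to Background and rationale {6a}, the pilot behind the ICC ran in poorer neighbourhoods of one city, so 0.046 probably holds little between-block variance to remove. The m of 25 matches the classroom groups of 20–40 in Study setting {9}, whereas the randomised unit is the school. The calculation ignores baseline adjustment. It also treats an overstated standard error as lost true precision, although stratified allocation already delivers the precision.

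Nor can a reader infer that the arms are unbalanced on state/private. Trial design {8} claims stratification and reports no balance.

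**Conclusion.** The contradiction is certain from the text: three factors in {8}, two in the abstract and {16a}, and three blocks that exclude funding status.

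The mismatch between allocation and model is real as the model is written, and its direction is known. The standard error is too large whenever blocks predict outcome beyond baseline, so actual alpha falls below 0.05 and some power is lost. A reader might conclude that the analysis is invalid or prone to false positives; the opposite holds.

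The size is not derivable, because the number of schools and the variance explained by blocks are not given and the pilot ICC comes from a narrow setting. The 3–5 points of power are an illustration that rests on 50 clusters of 25, 10% loss, R of 0.25–0.50 and no baseline adjustment. Fewer and larger schools would raise the figure, baseline adjustment would lower it, and at R = 0 it is zero. The change is worth making because it is nearly free and makes the analysis match the randomisation.

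**What to change.** 1. State one list of stratification factors, the one actually used in the allocation, identically in the abstract, Trial design {8} and Sequence generation {16a}. Enrolment began in August 2025, so this should record what was done.
2. In Statistical methods {20a}, add the randomisation block as a fixed effect in every primary and secondary outcome model: three levels under {16a}, plus funding status only if it was used. Keep the moderator interactions as separate analyses.
3. Date the amendment before the interim analysis of post-test data described in Interim analyses {21b}, since the trial is open-label.

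The cost is a text correction and one model term. Block membership is known at allocation, so no new data are needed. The statistical price is two school-level degrees of freedom for three blocks, or three if funding status enters as one further term. With about 50 clusters that is negligible; if schools are few it matters somewhat, so the number of schools should be weighed when the term is added.

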### Concealment mechanism {16b}

Allocation is not concealed and will be revealed to both participants and the research team after randomization.

### Implementation {16c}

An allocation sequence will be generated by the PI; they will assign schools to the intervention and control groups without knowing the name and exact location of the school. The study group will then be revealed to the research team and participating schools.

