**Discussion:**

Based on pilot data, we hypothesise that the intervention group will demonstrate increased media literacy and decreased body dissatisfaction at post-test and follow-up. We also anticipate improvements in secondary outcomes. This will be the first cluster RCT to evaluate the effect of a culturally adapted body image intervention in Colombia. This trial has been registered in the ISRCTN Registry (ISRCTN15802562, https://doi.org/10.1186/ISRCTN15802562). First enrolment was on 26th of August 2025.

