## Methods: participants, interventions, and outcomes

### Study setting {9}

This project will run full assessments of the effectiveness of the program with adolescents attending 7th to 10th grade (typically 11–17-year-olds) in urban and rural Northern Colombia. Trained facilitators (paid research assistants) and students will deliver materials during the school day. Schools will be recruited through word of mouth and researcher contacts. All intervention activities are classroom-based and will be delivered to mixed-gender groups of 20–40 participants during class time. Outcome assessments will also be completed during the school day, in classrooms. Materials have been refined based on prior pilot study data with adolescents in the city of Barranquilla (*N* = 338). Quantitative assessments will use a wait-list control design, with outcomes measured at baseline, immediate post-test, and follow-up (9–12 months later). We are using translated and validated scales to assess body image, sociocultural internalization, eating attitudes, and general wellbeing. Additionally, we are in the process of validating scales measuring appearance comparison, curvy ideal internalization, appearance-altering behaviours, and colourism attitudes. All scales have undergone psychometric evaluation and linguistic adaptation to ensure cultural relevance for the Colombian context in a sample of Colombian adults (*N* = 505; *M*_age_ = 21.48, *SD* = 2.96, range 18–30). 

In Colombia, all areas are classified into six socioeconomic strata (*estratos*) based on residents’ income and living conditions. *Estrato* 1 includes the lowest-income households, whereas *Estrato* 6 comprises the highest. This stratification system is used to determine public service subsidies and utility fees: lower strata receive financial assistance for basic services such as electricity and water, while higher strata pay increased rates to support social equity [12].

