## Oversight and monitoring

### Composition of the coordinating centre and trial steering committee {5d}

This study is being conducted across multiple secondary schools in Colombia, through a collaborative partnership between Universidad del Norte (Barranquilla, Colombia) and Durham University (UK). The project is jointly designed and implemented by both institutions. Day-to-day support is provided by the principal investigator and the UK research team, who oversee the overall trial management.

Data management is a shared responsibility between the Colombian and UK teams, with data securely stored on both institutions’ servers. The study coordinator, [name] [name], leads the organization of data collection, school visits, data entry, and secure data storage.

The research team holds weekly meetings in various subgroups to coordinate ongoing activities and convenes monthly as a full team to review trial progress. Communication is maintained continuously through WhatsApp and email.

An international advisory group, composed of experts in the field, meets twice a year to provide strategic guidance and oversight. The advisory group is independent of the study. Several members of the advisory group have extensive statistical knowledge.

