## Trial status

Recruitment has started on the 13th of August 2025. The current protocol is version 2 of the 4th of December 2025. Recruitment is estimated to be completed by August 2027.

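### Allocation of schools is declared unconcealed, and the sequence is held inside the trial team while that team is still recruiting schools

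*Protocol article*

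**What the plan says.** All references are to the protocol article.

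- **Concealment mechanism {16b}:** the whole entry reads "Allocation is not concealed and will be revealed to both participants and the research team after randomization".
- **Implementation {16c}:** on who draws and assigns, the article says "An allocation sequence will be generated by the PI; they will assign schools to the intervention and control groups without knowing the name and exact" (the sentence closes with the school's whereabouts). The arm is then made known to the research team and the schools.
- **Sequence generation {16a}:** random blocks by SES and area, "resulting in three different blocks: rural/low SES; urban/high SES; urban/low SES", with random assignment inside each. No block size or balance rule is given, and nothing says whether the schools of a stratum are drawn together or singly. Trial design {8} sets a 1:1 ratio and adds funding status as a further stratifier.
- **Who brings schools in:** Study setting {9} says "Schools will be recruited through word of mouth and researcher contacts". The consent section {26a} has the research team contact the schools.
- **The PI's other role ({5d}):** "Day-to-day support is provided by the principal investigator and the UK research team, who oversee the overall trial management". The same section describes an advisory group that is independent of the study and includes members with statistical expertise.
- **Timing:** Trial status says "Recruitment has started on the 13th of August 2025" and "Recruitment is estimated to be completed by August 2027". The abstract adds "First enrolment was on 26th of August 2025".
- **Order of consent:** Who will be blinded {17a} places parental consent before randomisation.

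**The concern.** Concealment and blinding are different protections. Blinding would keep people from knowing the arm after assignment, and an open classroom programme against a waitlist cannot provide it. Concealment keeps people from knowing or guessing the arm before a unit is irrevocably entered, and any open trial can provide it. The answer under {16b} gives up the second along with the first.

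The school is the randomised unit, and the research team influences which school enters and when. If that team can anticipate the next arm, a more cooperative or more favourable school can be put forward when the intervention is expected, even without intent. The resulting imbalance would lie between schools. Adjusting for each pupil's baseline score would remove only part of it, and both primary outcomes would be exposed.

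**Working it through.** **1. Who holds what, and when.**

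| Task or knowledge | Who | Section |
|---|---|---|
| Generates the sequence and assigns schools | PI | {16c} |
| Shares day-to-day support and trial management | PI | {5d} |
| Finds and contacts schools | Research team | {9}, {26a} |
| Learns each allocation once made | Research team | {16b}, {16c} |
| Recruitment window | 13 August 2025 to about August 2027 | Trial status |

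Sequence, management and recruitment all sit within one team, and past allocations are open to it. Nothing in the text separates the holder of the sequence from those who put schools forward.

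**2. What the stated safeguards cover.**

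- The PI does not know the school's name and exact location. This limits deliberate matching of a school to an arm by the PI. It does not bind the recruiters.
- Parental consent comes first. This protects against parents consenting differently by arm within a school. It does not govern which school is brought forward next.

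**3. How predictable the next arm could be.** The plan gives no figure to reproduce, so this is a conditional calculation.

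Assumptions:
- Each stratum is one balanced 1:1 block of *k* schools, filled one school at a time.
- The guesser knows all earlier assignments in the stratum and names the arm with more places left.
- *k* is not in the document. Taking the sample-size section's 1250 participants and average group size of 25, 1250/25 = 50 groups. One to three groups per school gives about 50 to 17 schools, or about 16 to 6 in each of three strata.

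Formulas:
- Expected correct guesses = k/2 + (2^k / C(k, k/2) − 1)/2.
- Expected number of assignments already certain before they are made = 2k/(k + 2).

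| k | Correct guesses | Share correct | Certain assignments |
|---|---|---|---|
| 6 | 3 + (64/20 − 1)/2 = 4.10 | 68% | 12/8 = 1.50 |
| 8 | 4 + (256/70 − 1)/2 = 5.33 | 67% | 16/10 = 1.60 |
| 16 | 8 + (65536/12870 − 1)/2 = 10.05 | 63% | 32/18 = 1.78 |

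Enumerating all balanced sequences gives the same values. Chance is 50%.

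If funding status were also applied as a stratifier, as {8} says but {16a} does not, blocks would be smaller. For k = 4, correct guesses are 2 + (16/6 − 1)/2 = 2.83, or 71%.

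**4. The other readings.** With simple randomisation inside each stratum, or with all schools of a stratum drawn together, past assignments carry no information: 50% correct and none certain.

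**The case against.** A reader might infer that upcoming assignments can be predicted in this trial, and that the last ones in each stratum are certain. The documents do not support that. {16a} uses the word blocks for what are in effect the strata and states no balance rule. Trial status dates recruitment, not randomisation. First enrolment 13 days after recruitment opened makes a single draw at the end hard to picture, but waves within strata remain possible. An article may leave block size and timing to a fuller document, so their absence is not itself a fault. This part of the objection stands, and the figures above are therefore only conditional.

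It can also be said that the sentence in {16b} merely describes openness after randomisation. That is probably what was meant. It is still the article's whole answer on concealment, and it states that there is none.

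No text says that the PI chooses which school is approached, or that the list is shared. The number of schools per stratum is not given either, so it cannot be shown that the stratum would reveal a school to the PI. That stands too. What remains is that the sequence is not held independently and that the recruiting team sees every past result.

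Finally, the order of consent before randomisation already supplies part of what concealment requires. It does, but for pupils within a school rather than for the choice and order of schools.

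**Conclusion.** The weakness is a written design choice: allocation is declared unconcealed, the PI who shares trial management generates the sequence and assigns schools, and the team recruiting through its own contacts learns each result during a window of about two years. It should be corrected for the schools still to come.

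Its size is conditional. Under single balanced blocks filled one school at a time, with 6 to 16 schools per stratum, a guess is right for about 68% to 63% of schools, and about 1.5 to 1.8 assignments per stratum are certain. Under simple randomisation or full batching, there is no prediction from past assignments.

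A reader might go on to turn these percentages into a bias in SD units. The documents do not allow it. That step needs the strength with which recruiters would steer schools, for which nothing is given, and a pool of schools ready to be reordered. The stated ICC of 0.046 accompanies an average group size of 25 and is not shown to be a between-school value. No bias size is claimed here.

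**What to change.** For schools not yet randomised, replace the text of {16b} and {16c} as follows:

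1. Someone outside recruitment and trial management generates and holds the sequence. A member of the existing independent advisory group with statistical expertise would serve.
2. A school's arm is released only after the school, its stratum, its participating classes and its list of consenting families are fixed.
3. Schools are randomised in batches within stratum. Where a school must be randomised alone, block sizes vary at random and are not disclosed to the team.
4. The text states that allocation is concealed until assignment and open afterwards.
5. The trial reports how the schools already randomised were assigned, including the block rule and whether they were drawn singly or together.

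The lists of stratifiers in {8} and {16a} should be reconciled at the same time, since they determine block size.

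The cost is protocol wording and a small task for an existing adviser, with no extra participants. Some schools may wait a short time for their batch, and varied blocks may leave an imbalance of about one school per stratum.
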